#### Assessments to adjust per-protocol analysis

The per-protocol analyses will be adjusted based on a new approach proposed by Miguel Hernán [36] with the following a priori specified factors: 1) *Prognostic factors for the primary outcome dyspnoea*, 2) *Adherence to conduct the exercises*, and 3) *Information whether the participants conducted other strengthening exercise trainings* (for details see chapter Statistical analyses). Besides the prognostic factors which are already assessed by routinely planned measurements, we will additionally assess self-efficacy to conduct the exercise training and information on other exercise strength trainings by the participants.

#### Cost-effectiveness outcomes

We will conduct health economic analysis comparing the relative costs and outcomes (effects) of the intervention and the comparator. Outcomes are assessed after 3, 6 and 12-months and include *1) Direct healthcare costs* (patient-reported: physician visits, specialist visits, number of hospitalisations, total number of hospitalisation days, number of days in rehabilitation / study-staff-reported: costs of working hours (administration of the intervention, trainings, supervision of the intervention), costs of intervention material (elastic bands, training book); *2) Direct non-healthcare costs* (patient-reported: ambulance transportations to hospital (travel costs to usual physician visits are not considered), nursing home care); and 3) *Indirect costs; mainly productivity loss costs* (patient-reported: working status and disability status due to COPD, workdays lost due to COPD and related adverse events).

### Study visits and procedures

In the course of the study, assessment visits are planned at baseline (one visit for HOMEX-1 [T1] and two visits for HOMEX-2 [T0 and T1]) and at 12-months follow-up (T4). The visits are conducted by trained study nurses at the same location; for HOMEX-1 at the PR clinics where the study participants were recruited, for HOMEX-2 at the EBPI in Zurich. In addition, after 3 (T2) and 6 (T3) months a questionnaire including the CRQ, cost-effectiveness outcomes, assessment of other exercise trainings and prognostic factors for dyspnoea will be sent by mail to all participants. At 6 months follow-up, study staff will additionally call the participants to verify in depth responses regarding cost-effectiveness and other exercise training. Figure 1 (1a: HOMEX-1, 1b: HOMEX-2) shows the study flow per participant and the time schedule of study visits, assessments and intervention.

**Fig. 1 Fig1:**
[figure not shown]
Study flow per participant and overview on time schedule of study visits, assessments and intervention (1a: HOMEX-1, 1b: HOMEX-2)

### Randomisation

Participants will be randomised for each HOMEX-trial separately, on the level of participants, with a 1:1 ratio, using block randomisation with varying block sizes, stratified by numbers of repetitions in the 1-min STS test (≤19 vs. > 19 repetitions) and, for HOMEX-1 only, additionally stratified by study centre. Randomisation is performed by means of Research Electronic Data Capture (REDCap) [37], a secure, web-based application specifically designed to support data capture for research studies which ensures concealment of random allocation. A biostatistician from the EBPI who is not involved in the study created for both HOMEX-trials a separate randomisation list using nQuery Advisor® + nTerim® 4.0 (Statsols, Cork, Ireland). Another independent researcher from the EBPI implemented these lists into the REDCap database. Randomisation will only take place after all baseline assessments are completed.

### Blinding procedures

Due to the kind of intervention, neither participants nor health care professionals can be blinded after the participants’ assignment to the intervention or control group. Data analysts will be blinded to group assignment.

### Withdrawal/discontinuation of participants

If a participant withdraws consent, the primary reason for this decision will be recorded. The exercise training programme will be discontinued and no further assessments conducted. If a participant is unable to continue the intervention for an extended period of time (assessed by the investigators regarding the specific participant and bearing in mind the participant’s personal situation), the participant is not considered withdrawn from the study. If he/she agrees, 12-months follow-up assessments will be conducted; if he/she refuses, follow-up assessments will be conducted at the time of discontinuation. Compliance/adherence to the study intervention will be analysed by evaluation the training books, the conduct of the home visits and regular phone calls and the records of the coaches’ reports.

### Data management

Data will be collected and managed using REDCap database hosted at the Clinical Trials Center (CTC) at the University Hospital Zurich, Switzerland. Study nurses, coaches and designated investigator site staff will enter the data; they will not be given access to the system until they have been trained. Automatic validation procedures within the system check for data discrepancies during and after data entry and, by generating appropriate error messages, allow the data to be confirmed or corrected online by the designated investigator site staff.

### Monitoring and quality assurance

All study nurses are trained before study onset, a second training will take place prior to the first 12-months follow-up visit. EBPI study staff will conduct three monitoring visits at each study centre; one 4 to 8 weeks after the conduction of the first baseline visit, a second after completion of all baseline assessments and a third after completion of all 12-months follow-up assessments. During these visits, the monitor will participate in one visit and verify whether the participants’ instruction, data assessment and randomisation are conducted according to protocol and check whether study procedures, documentation and REDCap data entry are conducted correctly. The monitor will check data entries of the primary and secondary outcomes in the REDCap database. The monitoring records are discussed with the Principal Investigator and, if necessary, procedures are derived to improve the quality of data collection, processes, documentation and data entry.

All coaches are fully trained before intervention onset. During the intervention a regular exchange between coaches takes place by a protected forum. In addition, every 3 to 6 months meetings with all coaches are conducted for exchange purposes. The master coach accompanies all coaches during one of their first home visits, checks whether the elements of home visits have been carried out according to the protocol and gives feedback to the coaches.

### Sample size

For each of the two trials, the sample size calculation is based on the primary outcome change in the CRQ dyspnoea domain from baseline to 12-months follow-up. For HOMEX-1, the hypothesis is maintenance in intervention group and decline in control group; for HOMEX-2, the hypothesis is improvement in the intervention group and maintenance in control group. The well-established minimal important difference of the CRQ dyspnoea scale is 0.5 [38]. Assuming a standard deviation of the outcome variable of 0.9 [2] (according to the literature we assumed the same standard deviation of CRQ dyspnoea outcomes for both patient populations, for those recently completing PR and for those who did not complete PR within the last 2 years), 80% power and a significance level of 5% (two-sided), a sample size of 52 patients in each group is required which results in a total sample size of 120 per trial, including a drop-out rate of 15% (patients for whom follow-up assessments are not possible; sample size calculator: http://hedwig.mgh.harvard.edu/sample_size/js/js_parallel_quant.html).

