### Statistical analyses

Analyses are conducted per trial separately. Baseline characteristics of the study participants are summarised according to numbers and percentages for qualitative variables, mean and standard deviation for quantitative variables with normal distribution and median and 25th–75th percentiles for quantitative variables with non-normal distribution. Differences in the change of the primary outcome CRQ dyspnoea from baseline to 12-months follow-up between the intervention and control group participants are compared by linear regression analyses corrected for stratification variables and, if deemed necessary due to baseline imbalances, potential confounders. The same analyses are used for continuous secondary outcomes. Changes in CRQ dyspnoea over the course of the year (assessed at 3, 6 and 12 month) will be examined using linear mixed models. The exploratory outcomes compliance to the training, satisfaction and health professionals’ feedback as well as the implementation process parameters will be analysed with a mixed-methods approach (using quantitative and the appropriate qualitative methods). If there is a substantial amount of missing values, we will compare the results from the complete case analysis with the results from a multiple imputation approach.

For the main analyses, we will use an intention-to-treat approach, i.e., the study participants will be analysed according to the group which they were originally randomised to, regardless of whether they adhered to the intervention according to protocol. Missing follow-up data of participants who did not conduct 12-months follow-up assessments will be substituted by the last available measurement (last observation carried forward).

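### The stated 52 per group, 15% drop-out and 120 per trial do not quite agree: 120 less 15% leaves 102 evaluable, two short of 104

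*Protocol article*

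**What the plan says.** The Sample size section of the protocol article gives one calculation, used for each of the two trials and based on change in the CRQ dyspnoea domain from baseline to 12 months. Its inputs are:

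- Difference: "The well-established minimal important difference of the CRQ dyspnoea scale is 0.5".
- Spread: "Assuming a standard deviation of the outcome variable of 0.9".
- Error rates: "80% power and a significance level of 5% (two-sided").

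From these it concludes that "a sample size of 52 patients in each group is required". The number to be randomised is then given in these words: "which results in a total sample size of 120 per trial, including a drop-out rate of 15" per cent. Drop-outs are defined in the same sentence as "patients for whom follow-up assessments are not possible". Allocation is equal (Randomisation section: "on the level of participants, with a 1:1 ratio, using block randomisation with varying block sizes").

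The Statistical analyses section adds that, in the main intention-to-treat analysis, missing 12-month data "will be substituted by the last available measurement (last observation carried forward").

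**The concern.** The sentence presents 120 as the number that still provides the required 52 per group once 15% have been lost. A reader who takes 15% off 120 arrives at 51 per group instead. The requirement, the drop-out rate and the total therefore cannot all be right as written.

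What is at stake is whether a stated figure can be reproduced, and how much loss each trial can bear before it falls below its own target. Because one calculation serves both trials, the mismatch appears in both.

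**Working it through.** **Inputs.** Difference 0.5 (stated as the minimal important difference and taken here as the target difference), SD 0.9, two-sided alpha 0.05, power 0.80, required evaluable number 52 per group (104 in total), drop-out 15% and total 120, all from the Sample size section. Allocation 1:1 is from the Randomisation section.

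**Step 1: reproduce the 52.**

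- Normal approximation: n per group = 2 x [SD x (z0.975 + z0.80) / difference]^2 = 2 x [0.9 x (1.960 + 0.842) / 0.5]^2 = 50.86, so 51.
- Two-sample t-test (noncentral t, noncentrality = 0.5 / (0.9 x sqrt(2/n)), 2n - 2 degrees of freedom): power is 79.3% at n = 51 and 80.1% at n = 52, so 52 is the smallest n that reaches 80%.

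The stated 52 is thus the t-test answer, and this first half of the calculation is correct.

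**Step 2: apply the stated drop-out to the stated total.**

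- Evaluable: 120 x (1 - 0.15) = 102, or 51 per group.
- Required: 2 x 52 = 104.
- Shortfall: 2 evaluable patients, one per group.

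**Step 3: work back from 104.**

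- Randomised number needed at 15% loss: 104 / 0.85 = 122.4, so 123, or 124 as two groups of 62. That is 3 to 4 more than 120.
- Largest loss that 120 can bear while keeping 104: (120 - 104) / 120 = 16 / 120 = 13.3%.

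**Step 4: where 120 might come from.**

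- 104 x 1.15 = 119.6, which rounds to 120.
- 102 / 0.85 = 120 exactly, starting from 51 per group.

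The article shows neither step, so the origin stays open. Step 2 does not depend on it.

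**Step 5: effect on power if 15% are lost.**

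| Evaluable per group | t-test | Normal approximation |
|---|---|---|
| 52 (as required) | 80.1% | 80.9% |
| 51 (120 less 15%) | 79.3% | 80.1% |

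**The case against.** Four points can fairly be made for the plan.

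*A drop-out allowance was made.* This stands. Sixteen patients were added to 104. A reader might infer that drop-out was ignored, but the text does not support that: the allowance is there and is short by two evaluable patients.

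*Under the normal approximation, 120 is exactly right.* That formula gives 51 per group, 102 / 0.85 is 120, and power at 51 is 80.1%. This shows that the practical consequence is negligible. It does not repair the sentence, because the article states 52 as the requirement, and 52 is the t-test figure. Starting from 51 replaces the article's own number.

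*The main analysis carries the last observation forward, so up to 120 patients could be analysed.* It is true that 102 describes patients with a 12-month outcome and not necessarily everyone in the main analysis. But the sample size is inflated precisely because drop-outs do not count towards the 52; if carried-forward values counted in full, no inflation would be needed. Nor do such values restore the missing 12-month information. A patient with no follow-up at all would contribute a change of zero. Under the stated hypotheses (intervention group maintained and control group declining in HOMEX-1; intervention group improving and control group maintained in HOMEX-2), zeros among HOMEX-1 controls or HOMEX-2 intervention patients would pull the groups together.

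*The difference is far smaller than the uncertainty in the assumed SD.* This is a fair argument about importance. The SD of 0.9 is taken from the literature and applied to two different populations, and its uncertainty could matter more than one patient per group. It bears on how serious the mismatch is, not on whether it exists.

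**Conclusion.** The point holds as a small internal inconsistency. With 15% lost, 120 per trial yields 102 evaluable patients against a stated requirement of 104; equivalently, 120 supports about 13% loss, not 15%.

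The conclusion rests on the article's own definition of drop-out and on its own requirement of 52. The power figures also assume a true difference of 0.5, an SD of 0.9 and equal losses in the two groups.

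Two stronger readings are tempting and are not supported. One is that the trials are underpowered: at 15% loss, power is 79.3% or 80.1% depending on the formula, less than one point from target, and at a loss of 13.3% or less the t-test target is met. The other is that the authors multiplied by 1.15 where they should have divided by 0.85: the numbers fit that explanation, but the article does not show the step. Severity is low, and only the wording of a stated figure is affected.

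**What to change.** Keep 120 per trial and correct the sentence in one of two ways:

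- state that 120 allows for about 13% drop-out from the required 104; or
- keep 15% drop-out and state that 51 per group would then be evaluable, with power of about 79% by the t-test.

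Either version makes the requirement, the loss and the total agree for both trials. The cost is one sentence: no extra patients and no change to the design or the analysis. The only drawback is that the stated drop-out margin or power looks slightly less favourable.

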### Statistical analyses

Analyses are conducted per trial separately. Baseline characteristics of the study participants are summarised according to numbers and percentages for qualitative variables, mean and standard deviation for quantitative variables with normal distribution and median and 25th–75th percentiles for quantitative variables with non-normal distribution. Differences in the change of the primary outcome CRQ dyspnoea from baseline to 12-months follow-up between the intervention and control group participants are compared by linear regression analyses corrected for stratification variables and, if deemed necessary due to baseline imbalances, potential confounders. The same analyses are used for continuous secondary outcomes. Changes in CRQ dyspnoea over the course of the year (assessed at 3, 6 and 12 month) will be examined using linear mixed models. The exploratory outcomes compliance to the training, satisfaction and health professionals’ feedback as well as the implementation process parameters will be analysed with a mixed-methods approach (using quantitative and the appropriate qualitative methods). If there is a substantial amount of missing values, we will compare the results from the complete case analysis with the results from a multiple imputation approach.

For the main analyses, we will use an intention-to-treat approach, i.e., the study participants will be analysed according to the group which they were originally randomised to, regardless of whether they adhered to the intervention according to protocol. Missing follow-up data of participants who did not conduct 12-months follow-up assessments will be substituted by the last available measurement (last observation carried forward).

As a sensitivity analysis, we will additionally conduct a per-protocol analysis, where we will keep only those participants in the intervention group who adhered to the intervention in terms of conducted exercise trainings [36]. We define adherence to protocol as “conduct of exercise training sessions at least during 70% of the weeks within the year of intervention the participants were able to train at least during 4 times a week”, i.e., weeks when participants suffered from pulmonary exacerbations or other serious health conditions that prevented them from training are not considered; as discussed with the coach (definition of a fulfilled individualised training session per day [according to protocol: 3 different exercises per day are planned]: conduct of at least 2 different exercises per day / definition of a fulfilled week of training [rate of training sessions according to protocol: 6 per week]: conduct of at least 3 out of the planned 6 individualised training sessions per week on average).

We will adjust the per-protocol analyses with prognostic factors for the primary outcome dyspnoea (dyspnoea, lung function [FEV_1_], exercise capacity and events of exacerbations) and for adherence to conduct the exercises (self-efficacy to conduct the exercises, exercise capacity, dyspnoea and acute worsening of health state [exacerbations and other]) and with the information whether the patients conducted other exercise strength trainings. Concerning the control group, we will collect as much information as possible, especially with respect to the type and frequency of self-organised exercise training. This will also be included in the per-protocol analysis.

The cost-effectiveness of the intervention and comparator will be assessed as cost per quality-adjusted life year (QALY) gained. The analysis will be performed using a time horizon of one year (i.e., equal to the maximal follow-up of the trial) and using a societal perspective. No interim analyses are planned.

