#### Primary outcome

The primary outcome is the change in dyspnoea, measured by the Chronic Respiratory Questionnaire (CRQ) dyspnoea domain (standardised version, self-administered) from baseline until 12-months follow-up [24]. The CRQ dyspnoea domain is one of the most commonly used dyspnoea instrument in trials of PR and contains five questions responded on a 7-point Likert-type scale ranging from 1 (most severe dyspnoea) to 7 (no dyspnoea).

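### Baseline CRQ dyspnoea is not a fixed covariate in the primary change-score regression, and other covariates enter only on observed imbalance: a free gain in precision is left unused

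*Protocol article*

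**What the plan says.** The Primary outcome section defines the endpoint as a change score: "The primary outcome is the change in dyspnoea, measured by the Chronic Respiratory Questionnaire (CRQ) dyspnoea domain", taken from baseline to 12 months. Under Statistical analyses the arms are compared by "linear regression analyses corrected for stratification variables and, if deemed necessary due to baseline imbalances, potential confounders". The next sentence extends the model: "The same analyses are used for continuous secondary outcomes".

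The Randomisation section shows what is fixed by this. Allocation is "stratified by numbers of repetitions in the 1-min STS test" (19 or fewer against more than 19) and, "for HOMEX-1 only, additionally stratified by study centre". Neither variable is CRQ dyspnoea, so its baseline value can enter the primary model only through the imbalance clause.

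Later in Statistical analyses, dyspnoea is listed in advance among the prognostic factors for the primary outcome, but that adjustment is fixed only for the per-protocol sensitivity analysis. Blinding procedures states that the data analysts are masked to allocation.

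**The concern.** Two features of one sentence are at issue.

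First, a change score that is not adjusted for baseline subtracts the whole baseline value. Where the regression of follow-up on baseline has a slope below 1, this over-corrects. The arm that happens to start better will tend to show less improvement, and part of any chance baseline difference passes into the treatment estimate. Including the baseline value removes that part and reduces the residual variance.

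Second, under concealed randomisation a baseline imbalance is chance. Whether a covariate is worth adjusting for depends on its relation to the outcome, not on whether it looks unbalanced. A rule triggered by imbalance makes the primary model depend on the data and may leave out a prognostic covariate that looks balanced.

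At stake is the precision of the primary comparison in two trials of 120 participants each, and a primary model that can be named before the data are seen.

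**Working it through.** **Inputs from the Sample size section.** Target difference 0.5 ("The well-established minimal important difference of the CRQ dyspnoea scale is 0.5"); SD 0.9; two-sided alpha 5%; power 80%; 52 per group; 120 in total with 15% dropout. Evaluable per arm: 60 × 0.85 = 51.

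**Assumed inputs.** The correlation rho between baseline and 12-month CRQ dyspnoea is not given, so the range 0.3 to 0.8 is shown. The section attaches 0.9 to the outcome variable; this is read as the SD of change.

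**Reproducing the plan.** n per arm = 2 × (1.960 + 0.842)² × 0.9² / 0.5² = 50.9, so 51 by the normal approximation. The t-test version gives 51.84, so 52 as stated. Power with 51 per arm and no baseline adjustment is 79.3% (noncentral t) or 80.1% (normal approximation).

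**Effect of adjusting, equal SDs s at both times.** Var(change) = 2s²(1 − rho). Residual variance given baseline = s²(1 − rho²). Ratio = (1 + rho)/2. The residual SD is 0.9 × √ratio. Equivalent n is 51/ratio. Power is by noncentral t.

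| rho | variance ratio | residual SD | power at 51 per arm | equivalent unadjusted n per arm |
|---|---|---|---|---|
| 0.3 | 0.65 | 0.73 | 93% | 78 |
| 0.5 | 0.75 | 0.78 | 89% | 68 |
| 0.7 | 0.85 | 0.83 | 85% | 60 |
| 0.8 | 0.90 | 0.85 | 83% | 57 |

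The normal approximation gives 94%, 90%, 86% and 84%, against 80% unadjusted. A simulation of 20,000 trials agreed: 79% against 89% at rho 0.5, and 79% against 85% at rho 0.7.

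**Unequal SDs.** With k = follow-up SD / baseline SD, the ratio is (1 − rho²)k² / (1 + k² − 2·rho·k). At rho 0.7:
- k = 0.9: 0.4131/0.55 = 0.75, power 89%.
- k = 1.1: 0.6171/0.67 = 0.92, power 82.5%.
- k = 1.2: 0.7344/0.76 = 0.97, power 80.7%.

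The gain almost disappears as rho·k approaches 1: at rho 0.8 and k = 1.2 the ratio is 0.5184/0.52, just under 1. The ratio never exceeds 1, so apart from one degree of freedom adjustment does not lose precision.

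**Exposure to chance imbalance, equal SDs.** The unadjusted estimate moves by (1 − rho) times the baseline difference, against the arm that starts better. The baseline SD is 0.9/√(2(1 − rho)), and one standard error of the baseline difference is that SD × √(2/51).
- rho 0.5: SD 0.90, SE 0.178, shift 0.5 × 0.178 = 0.089, or 18% of 0.5.
- rho 0.7: SD 1.16, SE 0.230, shift 0.3 × 0.230 = 0.069, or 14% of 0.5.

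**Type I error, same simulation.** Either model fixed in advance gives about 5%. Adding baseline only when the imbalance has p < 0.10 (an assumed rule) gives 4.0% at rho 0.5 and 4.6% at rho 0.7. Picking whichever of the two models has the smaller p-value gives about 7%.

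**If 0.9 is instead the SD of a single score** (normal approximation, 51 per arm), unadjusted against adjusted power is 66% against 84% at rho 0.3, 80% against 90% at 0.5, and 95% against 97.5% at 0.7.

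**The case against.** The planned analysis is sound on its own terms. The trials are sized on the change score and analyse the change score. Over repeated randomisations the estimate is unbiased, and its standard error already includes the variation due to chance baseline differences. On the change-SD reading the 80% target is met without adjustment. All of this stands, and it limits the point to an improvement.

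A reader might infer that the imbalance clause inflates the false-positive rate. The document does not support that. Its trigger is imbalance, not the result; a rule of that kind came out slightly conservative in the simulation; and the analysts are blinded. The 7% figure requires choosing the more favourable model, which the document does not describe. Blinding does not fix the model, however, since imbalance and both fits can be seen with masked labels.

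It can also be said that a condensed article may leave the list of confounders and the imbalance criterion to the full protocol or analysis plan. That is fair, and their absence is not part of this point. The same holds for baseline handling in the linear mixed model, on which the article is silent. What remains is what the article does state: a fixed covariate set without the baseline value, and observed imbalance as the ground for adding to it.

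Finally, a marked imbalance in baseline dyspnoea could bring it in through the clause. That covers only the visible cases, and the gain in precision does not depend on imbalance being visible.

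**Conclusion.** The point holds as a free improvement, not as an error that invalidates either trial. The stated primary model omits the baseline value of its own outcome and lets observed imbalance decide on further covariates.

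The direction of the precision loss is certain. Its size is not, because it rests on rho and on the ratio of SDs, neither of which is in the document. With equal SDs and 0.9 as the SD of change, power at 51 per arm would rise from about 79% to between 93% (rho 0.3) and 83% (rho 0.8). With a follow-up SD 1.2 times the baseline SD and rho 0.7 it would reach only about 81%.

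Two further readings are tempting and should not be drawn. The design is not shown to be underpowered; a shortfall appears only if 0.9 is the SD of a single score and rho is below about 0.5. Nor does the document say that baseline dyspnoea is the strongest predictor of change. It lists it as one prognostic factor among several.

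**What to change.** In Statistical analyses, state that the primary outcome and each continuous secondary outcome are compared between arms by linear regression adjusted for the baseline value of that outcome and for the stratification variables. Remove the imbalance clause from the primary model. If adjustment for other covariates is wanted, place it in a labelled sensitivity analysis.

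The treatment coefficient is the same whether the dependent variable is the change or the 12-month score once baseline is in the model, so the definition of the primary outcome need not change. The cost is one sentence and one degree of freedom. Baseline assessments are already completed before randomisation, so nothing changes in data collection, sample size or schedule. The change should be made before any comparison by arm, and recorded as an amendment.

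### The main intention-to-treat analysis carries the last dyspnoea value forward to month 12 although each trial's hypothesis is change in one arm, so the primary estimate is expected to be biased, in a direction not known in advance

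*Protocol article*

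**What the plan says.** The Statistical analyses section compares the arms on 12-month change in CRQ dyspnoea by linear regression. It then sets the main approach: "For the main analyses, we will use an intention-to-treat approach", and fixes the missing-data rule directly after it: "Missing follow-up data of participants who did not conduct 12-months follow-up assessments will be substituted by the last available measurement (last observation carried forward").

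The paragraph before has a second provision. If missing values are substantial in amount (no threshold is given), "we will compare the results from the complete case analysis with the results from a multiple imputation approach". The same paragraph plans a linear mixed model for CRQ dyspnoea at 3, 6 and 12 months, but only for the secondary time-course outcome.

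The Sample size section states what each trial expects. For patients who have just finished rehabilitation it says: "For HOMEX-1, the hypothesis is maintenance in intervention group and decline in control group". For patients without recent rehabilitation the expectation differs: "for HOMEX-2, the hypothesis is improvement in the intervention group and maintenance in control group". The section plans for 15% drop-out.

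Two other sections determine which value gets carried. Under Study visits and procedures, the CRQ is mailed at 3 and 6 months. Under Withdrawal/discontinuation of participants, someone who cannot continue the intervention stays in the study and is offered the 12-month assessment; someone who refuses it is assessed when stopping.

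**The concern.** Carrying a value forward asserts that nothing changes after the last contact. In each trial the hypothesis says the opposite for one arm. In HOMEX-1 the expected benefit is absence of decline, so a baseline value carried in the intervention arm reproduces the hypothesised result, and one carried in the control arm hides the hypothesised decline. In HOMEX-2 a carried value can miss a later gain or preserve an early gain that has since faded. The article's own Background reports that effects seen at the end of rehabilitation had shrunk or disappeared by 12 months in earlier trials, so an early value is a doubtful stand-in for month 12.

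At stake is the headline estimate of both trials. The regression also treats carried values as real 12-month measurements, so the uncertainty about them does not enter the standard error.

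**Working it through.** **Inputs from the article (Sample size).** Target difference 0.5 ("The well-established minimal important difference of the CRQ dyspnoea scale is 0.5 [38"]), SD 0.9, 80% power, two-sided 5%, 52 per group, 120 per trial, 15% drop-out.

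**Assumed, because the article does not give them.** Drop-out by arm, when it occurs, the course over the year, and what happens to drop-outs afterwards. Ranges are shown.

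**1. The plan's own figure.** n = 2 × (1.96 + 0.84)² × 0.9² / 0.5² = 50.9, so 51 per group by the normal approximation. The t-test needs 52 (power 80.1%). 104 × 1.15 = 119.6, so 120. The stated figures are reproduced. With 15% of 120 lost, 102 remain, or 51 per arm.

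**2. Formula.** Let an arm have mean 12-month change m and drop-out proportion d. Let f be the share of the 12-month change already present in the carried value. The arm mean after carry-forward is m × [1 − d(1 − f)]. Baseline carried gives f = 0. With a linear course, the 3- and 6-month values give f = 0.25 and 0.5. Drop-out spread evenly over the three intervals gives an average f = (0 + 0.25 + 0.5)/3 = 0.25.

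**3. Drop-outs would have followed their own arm (true difference 0.50).** HOMEX-1: 0.5 × [1 − dC(1 − f)]. HOMEX-2: 0.5 × [1 − dI(1 − f)]. Subscripts I and C denote intervention and control.

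| Drop-out I / C | f | HOMEX-1 | HOMEX-2 |
|---|---|---|---|
| 15% / 15% | 0 | 0.425 | 0.425 |
| 15% / 15% | 0.25 | 0.444 | 0.444 |
| 15% / 15% | 0.5 | 0.4625 | 0.4625 |
| 10% / 20% | 0 | 0.40 | 0.45 |
| 10% / 20% | 0.25 | 0.425 | 0.4625 |

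**4. Intervention drop-outs lose the benefit.**
- HOMEX-2, 15% per arm, full early gain carried: truth 0.85 × 0.5 = 0.425, carry-forward 0.50, bias +0.075.
- HOMEX-1, 20% / 10%, baseline carried: truth 0.5 − 0.2 × 0.5 = 0.40, carry-forward 0.5 × 0.9 = 0.45, bias +0.05.
- HOMEX-1, 15% per arm, baseline carried: truth 0.425, carry-forward 0.425. The bias cancels.

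**5. HOMEX-1 with no effect, both arms declining 0.5.** False difference = 0.5 × (1 − f) × (dI − dC).

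| Drop-out I / C | Linear course (f = 0.25) | Baseline carried (f = 0) |
|---|---|---|
| 15% / 15% | 0 | 0 |
| 20% / 10% | 0.0375 | 0.05 |
| 25% / 5% | 0.075 | 0.10 |

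**6. Simulation** (20,000 to 40,000 trials per scenario, 60 per arm, SD of change 0.9, t-test on change; for the linear course, correlation 0.6 between visits). Mean estimates agree with the formulas.
- Type I error in step 5: about 5.6% (20%/10%) and 7.5% (25%/5%) with the linear course; about 6% and 10% with baseline carried.
- Power at a true 0.50 with 15% per arm: about 78% under carry-forward with either the linear course or baseline carried, against about 79% for complete cases, whose mean estimate was 0.50 when drop-out was unrelated to outcome.
- When half of each drop-out's own change was carried, power was about 84% although the estimate was only 0.46. The carried changes vary less than real 12-month changes would, so part of the apparent precision is artificial.

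**The case against.** **Exposure is limited by the design.** The CRQ is collected at 3 and 6 months, participants who stop training are still offered the 12-month visit, and those who refuse are assessed when they stop. A carried value can therefore already show decline. If a HOMEX-2 gain were complete by month 3, only the third of drop-outs carrying baseline would lose it: 0.5 × (1 − 0.15/3) = 0.475. The loss of power at equal drop-out is about one percentage point. All of this stands; it reduces the problem but does not remove it.

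**The plan already names multiple imputation.** It does, but conditionally, and it sets imputation against complete cases. Carry-forward is neither tested by that comparison nor replaced by it.

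Four stronger readings are tempting and are not supported:
- *That equal drop-out biases the estimate towards zero.* This requires drop-outs to follow their own arm's course. Step 4 gives +0.075 and zero with equal drop-out.
- *That every HOMEX-1 intervention drop-out is counted as a success and every control drop-out hides the decline.* This is fully true only if baseline is carried.
- *That two analysts would reach different primary results.* The text ties carry-forward to the main analysis, so the main rule is identifiable. What is unclear is how the complete-case and imputation analyses relate to it.
- *That values are carried past death.* The article is silent on deaths, and a condensed article may leave this to the full protocol or analysis plan.

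**Conclusion.** The concern holds in this form: a fixed rule for the main analysis contradicts the hypothesis in one arm of each trial, so the primary estimate is expected to be biased, with size and direction unknown in advance. If drop-outs would have followed their own arm, 15% drop-out per arm moves a true 0.50 to about 0.42 (baseline carried) or 0.44 (linear course, even timing). If intervention drop-outs lose an early gain, the shift can favour the intervention. In HOMEX-1 under no effect, with more loss in the intervention arm (20%/10% to 25%/5%), the false benefit is about 0.04 to 0.10, with type I error about 5.5% to 10%. The upper end needs both the 25%/5% split and baseline carried throughout. The unequal rates, the timing and the linear course are assumptions; only the overall 15% comes from the article. The main harm is a shifted estimate and possible false benefit rather than lost power.

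**What to change.** Replace carry-forward as the main rule, before outcome data are seen.

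1. Take the primary result from the 12-month between-arm contrast of the linear mixed model already planned for CRQ dyspnoea at 3, 6 and 12 months, adjusted for baseline score and stratification factors. Multiple imputation using the 3- and 6-month CRQ is an acceptable alternative. Either has an expected value of 0.50 for a true 0.50 if data are missing at random.
2. Use multiple imputation for outcomes measured only at baseline and 12 months.
3. Add one sensitivity analysis for data not missing at random, for example giving intervention drop-outs the control arm's course.
4. Keep carry-forward at most as a sensitivity analysis, and state how the complete-case and multiple-imputation analyses relate to the main one.

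The cost is new wording and some extra analysis, with no new data. The result will rest on missing-at-random, and the interval may be slightly wider than under carry-forward. The sample size does not change: 120 per trial already allows for drop-out.
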